### 4.2. Recruitment and Screening Procedure

Patients will be recruited from the movement disorder outpatient clinic at Neurocenter of Southerland Switzerland EOC, in Lugano. Graphical representation of the sequence of events is illustrated in Figure 2.

At screening, we will evaluate all aspects useful to satisfy the inclusion/exclusion criteria of the study. In this context, PD patients that satisfy Litvan’s diagnostic criteria for MCI [34] will undergo a clinical interview and questionnaires to ensure their ability to understand the instructions and to exclude the most severely depressed subjects. 

### 4.3. Main Inclusion and Exclusion Criteria

#### 4.3.1. Inclusion Criteria

Participants will be eligible for inclusion if they meet the following criteria:1.Age range
Participants must be aged between 50 and 75 years, a range chosen to reflect the population most affected by PD-related cognitive decline while minimizing age-related confounding factors.
2.Disease severity
A definitive clinical diagnosis of PD in accordance with the UK Parkinson’s Disease Society Brain Bank criteria [35];The severity of PD will be assessed using the Hoehn and Yahs scale, with eligible participants having a disease stage between 2 and 3, indicating moderate PD without severe motor complications;Participants must exhibit mild cognitive impairment (MCI) according to criteria of Litvan et al. 2012 [36], ensuring that cognitive decline is present but does not meet the criteria for dementia;No family history and no major cognitive impairment or major dysautonomic symptoms in history.
3.Medical stability
Participants must be on a stable dose of dopaminergic medications for at least three months prior to enrollment to reduce variability due to medication fluctuations;If applicable, antidepressant or anxiolytic medications must be maintained at a stable dose for at least two months prior to study participation.
4.Comorbid conditions
Apart from clinical diagnosis of PD, participants must be in good health, with no history of uncontrolled chronic conditions that could interfere with the study outcomes;Controlled comorbid conditions such as hypertensions or type 2 diabetes mellitus are permissible if they are well managed with medication and lifestyle measures.
5.Physical and functional status
Absence of significant postural instability or freezing-of-gait episodes that could interfere with participation in rTMS sessions.

#### 4.3.2. Exclusion Criteria

Participants will be excluded if they meet any of the following conditions:1.Advanced disease stages
Hoehn and Yahr stages ≥ 4, indicating severe disease progression with significant motor and cognitive impairment.
2.Neurological and psychiatric comorbidities
Any neurological condition other than PD;A history of major psychiatric disorders, including major depressive disorder (Beck Depression Inventory-II ≥ 29 [37] or active psychosis, which could confound cognitive assessments;Transient ischemic attack, stroke, or any unexplained loss of consciousness or severe ongoing stressor within 1 year prior to screening.
3.Contraindications to rTMS
Contraindication to treatment will be investigated using a standard safety questionnaire to screen potential subjects for risk of adverse events during TMS (Safety Questionnaire for TMS [38]);Presence of metallic implants, pacemaker, or other electronic medical devices that pose a safety risk during TMS session;History of epilepsy or seizure disorders, as determined by self-reporting and medical history.
4.Others
Any medical conditions that are not stable or controlled, or, which in the opinion of the Investigator, could affect the subject’s safety or interfere with the study assessments and treatment;Any medications that, in the opinion of the Investigator, may contribute to cognitive impairment, put the subject at higher risk for adverse events, or impair the subject’s ability to perform cognitive testing or complete study procedures.Use of illicit narcotic medication.

Patients who fulfill the inclusion criteria and do not meet any exclusion criteria will be asked to enroll in the project.

Once enrolled, patients will be randomly assigned to one of three groups: (1) R-Gr, (2) S-Gr, or (3) C-Gr. A computerized random number generator (www.random.org/sequences/, accessed on 24 January 2025) with concealment, with a 1:1:1 allocation, will be used for randomization. Blood collection and neurocognitive assessment will be performed at baseline, T1, and T2.

The assessment will be conducted in one session and it will take 60 min for each patient. Schedule of study procedures is reported in Table 1.

### 4.4. Power Analysis

The primary outcome measures will be plasma BDNF, plasmatic EV-derived BDNF, and BADS. We anticipate positive score changes in the R-Gr group, a minimal effect in the S-Gr group, and, aside from a slight learning effect regarding cognitive performance, no changes in the C-Gr group. This will effectively balance out in our analyses because we will compare changes in means across these groups.

We have estimated our sample size using G*Power 3.1 for a repeated-measures MANOVA with between-group factors. The parameters were set as follows: medium effect size (f = 0.25), significance level (α = 0.05), power (1 − β = 0.80), correlation among repeated measure (r = 0.1), 3 groups, and 3 repeated measurements. The calculation indicated a required total sample size of 66 participants (approximately 22 per group) to detect a significant difference between groups. To account for a 10% dropout rate, the adjusted total sample size will be 73 participants (approximately 24–25 per group). This sample size will ensure adequate power to detect clinically meaningful differences while accounting for potential attrition.

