## 5. Statistical Analyses

### 5.1. Primary Analyses

The baseline demographic, clinical, laboratory measures and cognitive scores will be compared between groups using an ANOVA for continuous variables and Chi-square tests for categorical variables. Covariates such as age and gender will be included if group differences exist at baseline.

A mixed-factorial ANOVA will be conducted to evaluate the effect of the rTMS protocol after 4 weeks of daily stimulation on plasma BDNF levels, the plasmatic EV-derived BDNF concentration, and EF performance. The model will include Group as a between-subjects factor and Time as a within-subjects factor.

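### Section 4.4 sizes the trial for group means averaged over three visits including baseline; 80% power for the planned comparison of 4-week change is not shown, and is not reached at the plan's own r = 0.1

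*Protocol article*

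**What the plan says.** Section 4.4 names the procedure ("We have estimated our sample size using G*Power 3.1 for a repeated-measures MANOVA with between-group factors") and its inputs: "medium effect size (f = 0.25), significance level (α = 0.05), power (1 − β = 0.80"), then "correlation among repeated measure (r = 0.1), 3 groups, and 3 repeated measurements". The result is a "required total sample size of 66 participants (approximately 22 per group) to detect a significant difference between groups". After an allowance for 10% dropout the total is 73. The section closes by asserting that this size gives enough power for clinically relevant differences.

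The same section describes the comparison differently: "we will compare changes in means across these groups". It expects improvement in the real-stimulation group, little effect under sham and, apart from some learning on the cognitive test, none without treatment.

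Sections 2.1.1 to 2.1.3 define all three primary outcomes as change after 4 weeks of treatment, with real rTMS compared against both sham and no treatment. Section 5.1 analyses the 4-week effect with a mixed-factorial ANOVA: "The model will include Group as a between-subjects factor and Time as a within-subjects factor". It does not list the levels of Time. The models on baseline and T2, and on all three visits, are in Section 5.2 as secondary analyses.

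**The concern.** Comparing change between groups is the Group × Time interaction. The G*Power between-factors option tests something else: whether the groups differ in their mean over all visits. Two features make this matter.

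- One of the three averaged visits is baseline. Randomisation makes the expected group difference there zero, so it dilutes any treatment effect in the average.
- The correlation r acts in opposite directions. A low r helps a test on averages, because the visits then carry more independent information. A low r hurts a test on change, because the variance of a change is proportional to 1 − r. The plan's r = 0.1 is given without justification. It is favourable to the test that was sized and unfavourable to the test that answers the question.

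If the power statement stands, readers will interpret a null result as if the trial had had an 80% chance of detecting a medium effect on change. The document does not establish that.

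**Working it through.** **Inputs.** From Section 4.4: f = 0.25, α = 0.05, r = 0.1, k = 3 groups, m = 3 measurements, N = 66 (22 per group). Allocation is 1:1:1 (Section 4.3.2). All F-test powers use the noncentral F distribution.

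**Step 1. Reproduce the plan's figure.** Between-factors test: λ = f²·N·m / (1 + (m − 1)r), df = 2 and N − 3.

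- N = 66: λ = 0.0625 × 66 × 3 / 1.2 = 10.31, power 0.808.
- N = 63: λ = 9.84, power 0.788.

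So 66 is the smallest multiple of three that reaches 80%. The other options tried do not give 66: the interaction option gives 60, the within-factor option 48, and the MANOVA interaction with f(V) = 0.25 gives 99.

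**Step 2. Express that alternative as a change.** Assume, in line with Section 4.4, that only the real group changes, by d SD at both T1 and T2. The three-visit group means are then 2d/3, 0 and 0, so f = (2d/3)·√(2/9). Setting f = 0.25 gives d = 0.795, about 0.80 SD.

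**Step 3. Power of the T0–T1 Group × Time test under the same alternative.** With two visits this is the one-way F test on change scores, whose variance is 2(1 − r): λ = 22·d²·(2/3) / (2(1 − r)), df = 2 and 63. At r = 0.1, λ = 22 × 0.633 × 0.667 / 1.8 = 5.16 and power is 0.497.

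| r | Test that was sized | T0–T1 Group × Time |
|---|---|---|
| 0.1 | 81% | 50% |
| 0.3 | 68% | 61% |
| 0.5 | 58% | 76% |
| 0.6 | 53% | 85% |
| 0.7 | 50% | 94% |

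The T0–T1 test crosses 80% at r ≈ 0.54. At r = 0.1 it would need 129 patients.

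**Step 4. Take f = 0.25 as the interaction effect instead.** λ = f²·N·m / (1 − r).

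- Two visits, r = 0.1: λ = 0.0625 × 66 × 2 / 0.9 = 9.17, df = 2 and 63, power 0.758. This corresponds to d = 1.06 SD if only the real group changes.
- Three visits, r = 0.1: λ = 0.0625 × 66 × 3 / 0.9 = 13.75, df = 4 and 126, power 0.845.

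Under the alternative of Step 2, the three-visit interaction has 51% power at r = 0.1 and 80% (79.9%) at r = 0.5.

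**Step 5. Detectable pairwise difference, 22 per group, two-sided 0.05, 80% power.** The multiplier from the noncentral t with 63 df is about 2.845.

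- Change contrast, δ = 2.845·√(2/22)·√(2(1 − r)): about 1.15 SD at r = 0.1, 1.02 at 0.3 and 0.86 at 0.5.
- Baseline-adjusted contrast, with √(1 − r²) in place of √(2(1 − r)): about 0.85, 0.82 and 0.74 SD. The plan does not contain this model.

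**The case against.** A reader might infer that the trial is underpowered whatever the correlation. The documents do not support that. Under the same alternative the T0–T1 test has 85% power at r = 0.6 and 94% at r = 0.7, and nothing in the article rules out correlations of that size. Convention matters too. Entering the stated f, r and m in the default three-visit interaction option gives 84.5% at 66 patients, and the two-visit version reaches 81% at r = 0.2. This part of the objection stands: the shortfall is conditional. It does not rescue Section 4.4, because the stated r is 0.1, the three-visit interaction is not the calculation that was made, f has a different meaning there, and that model is secondary.

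The reading of the primary model as T0 versus T1 is an inference, since Section 5.1 lists no Time levels. It rests on the 4-week outcome definitions and on the other two Time structures being assigned to Section 5.2. If the three-visit interaction were meant, power under the same alternative at r = 0.1 would still be only 51%.

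Three further readings go too far.

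- That only very large effects could be detected: the detectable change difference is 0.86 SD at r = 0.5, and falls further as r rises.
- That one pairwise contrast, real versus sham, decides the trial: Section 2.1 compares real rTMS with both other groups.
- That the dropout allowance is a material error ("To account for a 10% dropout rate, the adjusted total sample size will be 73 participants"): 66/0.9 = 73.3 rounds up to 74, but 73 × 0.9 = 65.7, and 65 evaluable patients still give 80.2% for the stated test.

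The number of primary outcomes and the error level applied to each is a separate issue and is not counted here.

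**Conclusion.** The concern holds as a mismatch between the sizing test and the primary analysis. The arithmetic in Section 4.4 is correct for the option named there, but that option tests a three-visit average, not change. For the T0–T1 Group × Time comparison, 80% power is not shown, and with the plan's own r = 0.1 and 66 evaluable patients it is not reached: about 50% under the same alternative and about 76% if f = 0.25 is taken as the two-visit interaction effect.

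These figures assume equal variances, the same r between visits, change in the real group only (for the 50%), and T0–T1 as the primary model. They do not show that the trial lacks power at every plausible correlation. They show that the claim of adequate power is unsupported until r is justified and the calculation matches the analysis.

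**What to change.** Rewrite Section 4.4, without extra enrolment:

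1. State power, or the detectable difference, for the planned T0–T1 Group × Time comparison with about 66 evaluable patients, with the effect defined on change.
2. Give it over a range of r and justify that range. For a pairwise change contrast, the Step 5 values (about 1.15, 1.02 and 0.86 SD at r = 0.1, 0.3 and 0.5) can be used directly.
3. Remove or qualify the closing assurance of adequate power.
4. List the Time levels and name the Group × Time term in Section 5.1.

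If the sponsor prefers a baseline-adjusted analysis, quote that model's smaller figures (about 0.85, 0.82 and 0.74 SD) and change Section 5.1 to match. Quoting them while keeping the mixed ANOVA would repeat the mismatch.

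The cost is a rewording and a less favourable power statement. Recruitment has begun (Section 6.3), so the change should be made before any outcome data are analysed, including at the interim analysis in Section 5.3.

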## 2. Primary and Secondary Outcomes

### 2.1. Primary Outcomes

#### 2.1.1. Change in Plasma BDNF Levels

We will evaluate the changes in plasma BDNF levels after 4 weeks of rTMS treatment in patients with PD-MCI compared to PD-MCI patients receiving sham rTMS treatment and those receiving no rTMS treatment.

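### The 80% power in 4.4 was computed for the Group main effect averaged over T0, T1 and T2, not for the between-arm difference in change from T0 to T1 that is the primary question

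*Protocol article*

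**What the plan says.** Section 4.4 of the protocol article describes the calculation as follows: "We have estimated our sample size using G*Power 3.1 for a repeated-measures MANOVA with between-group factors". The inputs are f = 0.25, alpha 0.05, power 0.80 and "correlation among repeated measure (r = 0.1), 3 groups, and 3 repeated measurements". The result is a "required total sample size of 66 participants (approximately 22 per group) to detect a significant difference between groups", raised to 73 for 10% dropout.

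The same section says that the learning effect will cancel "because we will compare changes in means across these groups". The primary outcomes in 2.1 are also about change. For plasma BDNF: "We will evaluate the changes in plasma BDNF levels after 4 weeks of rTMS treatment in patients with PD-MCI", compared with sham and with no treatment. EV-derived BDNF (2.1.2) and executive function (2.1.3) are worded in parallel.

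Section 5.1 plans a mixed-factorial ANOVA for the effect after 4 weeks: "The model will include Group as a between-subjects factor and Time as a within-subjects factor". It does not list the levels of Time. Section 5.2 places the baseline/T2 model and the baseline/T1/T2 model among the secondary analyses.

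**The concern.** A mixed ANOVA with Group and Time contains two different tests that involve Group. The Group main effect asks whether arm means differ when averaged over all visits in the model. The Group x Time interaction asks whether arms change differently. Only the second answers the primary question as 2.1 puts it.

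The wording of 4.4 (between-group factors, three measurements, a difference between groups) points to the first. One of those three measurements is baseline, where randomised arms have equal expected means. Including it in the average dilutes any treatment effect.

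If the sized test is not the primary test, the reader has no basis for the claim that 66 completers give 80% power on any primary outcome. A null result on change could then be read as coming from an 80%-powered comparison when no calculation shows that.

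**Working it through.** **Inputs.** From 4.4: f = 0.25, alpha = 0.05, r = 0.1, k = 3 groups, m = 3 measurements, N = 66. From 4.1 and 4.3.2: measurements at T0, T1 and T2, allocation 1:1:1. All powers are from the noncentral F distribution.

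**Step 1: reproduce the printed 66.** Group main effect: lambda = N f² m / (1 + (m − 1) r), df = 2 and N − 3.

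- N = 66: lambda = 66 × 0.0625 × 3 / 1.2 = 10.31; power 80.8%.
- N = 65: lambda = 10.16; power 80.2%.
- N = 64: lambda = 10.00; power 79.5%.

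The smallest N is 65, which is 66 in equal groups. The conventional Group x Time formula, lambda = N f² m / (1 − r) with df = (k − 1)(m − 1) and (N − k)(m − 1), does not give 66 with the same f and r. It needs 60 with three visits and 73 (75 in equal groups) with two. Wording and arithmetic both identify the main effect.

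**Step 2: what the sized test delivers when baseline means are equal.** Let f = 0.25 be the separation of arm means at the visits where the effect is present (r = 0.1, N = 66).

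- Effect at T1 and T2: averaged f = 0.25 × 2/3 = 0.167; lambda = 4.58; power 45%.
- Effect at T1 only: averaged f = 0.25 × 1/3 = 0.083; lambda = 1.15; power 14%.

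**Step 3: power of the T0-T1 Group x Time test.** With two visits this equals a one-way ANOVA on change. In units of the single-visit SD, the SD of change is √(2(1 − r)), so f_change = f_T1 / √(2(1 − r)), lambda = 66 × f_change², df = 2 and 63. Section 4.4 does not say on which contrast f = 0.25 is defined, so three definitions are shown:

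- A: f = 0.25 is the arm separation at T1.
- B: f = 0.25 is the three-visit average of an effect that lasts to T2, so f_T1 = 0.25 / (2/3) = 0.375.
- C: f = 0.25 is the conventional interaction effect size. With two visits the interaction effects are half the differences in change, so f_T1 = 0.50.

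| r | A | B | C |
|---|---|---|---|
| 0.1 (the plan's) | 24% | 50% | 76% |
| 0.5 (assumed) | 41% | 76% | 95% |

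Example, A at r = 0.1: f_change = 0.25 / √1.8 = 0.186; lambda = 66 × 0.186² = 2.29; power 24%.

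Other values of r are assumptions too. C reaches 80.8% at r = 0.2; A reaches 81% only at r = 0.8.

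**Step 4: three-visit interaction, in case 5.1 intends all visits.** Conventional f = 0.25, r = 0.1: lambda = 66 × 0.0625 × 3 / 0.9 = 13.75, df = 4 and 126; power 84.5%.

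**Step 5: detectable difference.** For 80% power with df 2 and 63, lambda = 10.11 and f_change = √(10.11 / 66) = 0.391. If real rTMS differs from two equal control arms by d SD at T1, then f_T1 = d√(2/9). Hence d = 0.391 × √(2(1 − r)) / √(2/9), which is 1.11 SD at r = 0.1 and 0.83 SD at r = 0.5. Under definition A, f = 0.25 corresponds to d = 0.25 / √(2/9) = 0.53 SD.

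**The case against.** The arithmetic in 4.4 is correct for the test it names, and the harsher figures come from definitions that the article does not state. In the usual interaction convention, the T0-T1 test has 76% power at the plan's own r and passes 80% at r = 0.2. If the unlisted Time levels in 5.1 are all three visits, the interaction has 84.5%, more than was printed. Higher r helps the interaction and hurts the main effect, which falls to 58% at r = 0.5 even with an undiluted f = 0.25. So the direction of the error is not fixed.

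This part stands. A reader might infer from the 24% that the trial is under-powered, or that no reading of f reaches 80%. The documents do not support either: they settle neither r nor f, and some readings exceed 80%.

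It can also be said that a mixed ANOVA of this kind is ordinarily read through its interaction, and that an article may leave the choice of term to a fuller plan. That is fair. Section 4.4 already says that changes will be compared, and nothing says the Group main effect will be reported as the treatment test. The silence of 5.1 is therefore mostly missing detail.

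What the objection does not reach is 4.4 itself, which says that changes will be compared and then prints the power of a test that is not about change.

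**Conclusion.** The stated 80% belongs to the Group main effect averaged over T0, T1 and T2. It is not the power of the primary comparison, a difference between arms in change from T0 to T1. Identification of the sized test rests on the wording of 4.4 and on exact reproduction of 66.

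At r = 0.1 even the sized test has about 45% power if f = 0.25 is present only at T1 and T2, and about 14% if present only at T1. For the T0-T1 Group x Time test with 66 completers, power ranges from 24% to 76% at r = 0.1 and from 41% to 95% at r = 0.5. These figures assume that the primary model uses T0 and T1, which 5.1 implies through its reference to 4 weeks and its contrast with 5.2 but does not state. They also assume equal expected baselines, a common SD and no missing data.

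The mismatch does not by itself prove under-powering. It shows that the article's assurance of adequate power is unsupported for the primary outcomes, and the figure is wrong as written for the use made of it.

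**What to change.** In 4.4, rerun the calculation for the Group x Time term at T0 and T1, or equivalently for the arm contrast in T1 change. State the contrast on which f is defined. Justify r, or show a range of values. Replace the 80% statement with the resulting power, or with the detectable difference, for 66 completers.

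In 5.1, add one sentence that names this term, and not the Group main effect, as the primary treatment test for each outcome, and list the Time levels.

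The cost is a rewritten paragraph and one sentence. N, visits and procedures need not change. The restated power may be lower or higher than 80%, depending on r and the definition of f. Recruitment has begun according to section 6.3, and 5.3 plans an interim look at efficacy at 50% enrolment, so the change is best made before that look.

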## 3. Materials

### 3.1. Laboratory Measurements, Neurocognitive Assessment, and TMS Intervention

#### 3.1.1. Blood Sampling

All the blood samples will be drawn in the morning after overnight fasting at three time points: before the start of rTMS intervention (baseline), within 1 week after the end of treatment (T1), and within 1 week after the maintenance period (T2).

Blood will be drawn by trained staff from the antecubital vein (gauge of needle: 21 G × ¾″ × 7″, BD Vacutainer, REF 367282; BD, NJ, USA) into 15 vacutainers to ensure sufficient sample collection. Possible confounders for BDNF levels such as sex, age, and BMI will be accounted by statistical analysis and by analyzing multiple measurements at different time points intra subjects.

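### The 80% power in Section 4.4 belongs to a group main effect averaged over three visits at an unsourced r = 0.1, not to the planned baseline-to-T1 Group × Time comparison, where the effect of r is reversed

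*Protocol article*

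**What the plan says.** Section 4.4 of the protocol article names the calculation as "G*Power 3.1 for a repeated-measures MANOVA with between-group factors". The inputs are "medium effect size (f = 0.25"), "significance level (α = 0.05"), "power (1 − β = 0.80"), "correlation among repeated measure (r = 0.1"), and "3 groups, and 3 repeated measurements". The result is given as "The calculation indicated a required total sample size of 66 participants (approximately 22 per group"), raised to 73 for 10% dropout. The section closes by promising that this size gives adequate power for clinically meaningful differences. No source, pilot value or range is given for r, and one value serves plasma BDNF, EV-derived BDNF and BADS.

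The same section says the groups will be compared on changes in means. Section 5.1 tests the 4-week effect with a mixed-factorial ANOVA, Group between subjects and Time within subjects. Section 5.2 keeps the baseline/T2 model and the three-visit model as secondary. Section 3.1.1 says BDNF confounders will be handled by statistical analysis and "by analyzing multiple measurements at different time points intra subjects".

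**The concern.** The correlation between visits acts in opposite directions on the two tests a repeated-measures design offers. For a group main effect averaged over visits, a low r helps: the readings behave as nearly independent, so averaging removes more noise. For a comparison of change, a low r hurts: the baseline tells little about the later reading, so subtracting it adds noise.

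Section 4.4 fixes r near zero, without support, and prints one power figure. If that figure comes from the main-effect run while the plan tests change, the reader is given the power of a different test, and the assurance that closes the section has nothing under it. The direction of the error also cannot be judged until both the test and the meaning of f are stated.

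**Working it through.** **Inputs.** From Section 4.4: f = 0.25, α = 0.05, k = 3 groups, m = 3 measurements, r = 0.1, N = 66. Values of r of 0.3, 0.5 and 0.7 are assumptions, because the document reports no visit-to-visit correlation for any outcome.

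**Step 1: reproduce the printed figure.** For the between-groups main effect, the noncentrality is λ = f²·N·m / (1 + (m − 1)r), with df = (k − 1, N − k).

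λ = 0.0625 × 66 × 3 / 1.2 = 10.31, df (2, 63), power 0.808. The smallest N reaching 80% is 65, which is 66 in equal groups; N = 63 gives 0.788. With the same inputs the three-visit Group × Time interaction needs 60 and the within-subject test needs 48. Of these, only the between-groups main effect gives 66, so it is the run that was made, and its arithmetic is correct.

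**Step 2: change only r in that run (N = 66).**

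| r | λ | Power | N for 80%, equal groups |
|---|---|---|---|
| 0.1 | 10.31 | 0.808 | 66 |
| 0.3 | 7.73 | 0.680 | 87 |
| 0.5 | 6.19 | 0.576 | 108 |
| 0.7 | 5.16 | 0.497 | 129 |

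**Step 3: the planned comparison, baseline and T1, N = 66, df (2, 63).** Two readings of f = 0.25 are possible.

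(a) G*Power's default for the interaction: λ = f²·N·m / (1 − r) with m = 2. At r = 0.1, λ = 0.0625 × 66 × 2 / 0.9 = 9.17.

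(b) f as the spread of the group means at T1 in single-visit SD units, with no baseline difference and equal variances: the change score has variance 2(1 − r) in single-visit units, so λ = f²·N / (2(1 − r)). At r = 0.1, λ = 4.125 / 1.8 = 2.29.

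| r | (a) λ | (a) Power | (b) λ | (b) Power |
|---|---|---|---|---|
| 0.1 | 9.17 | 0.758 | 2.29 | 0.243 |
| 0.3 | 11.79 | 0.860 | 2.95 | 0.303 |
| 0.5 | 16.50 | 0.953 | 4.13 | 0.409 |
| 0.7 | 27.50 | 0.998 | 6.88 | 0.625 |

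The two λ differ by a factor of four at every r. With no difference at baseline, a T1 effect splits into interaction terms of plus and minus half its size, so its interaction f is half the T1 f: 0.125 rather than 0.25. Both versions rise with r, against the direction in Step 2. At the plan's own r = 0.1, neither reaches 80%.

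**The case against.** A reader might infer from Step 2 that the trial has only 58% power. The documents do not support that. The 58% belongs to the main effect and to an assumed r = 0.5. For the planned comparison a higher r helps, and under reading (a) r = 0.5 gives 95%. The three-visit interaction under reading (a) already has 0.845 at r = 0.1, although Section 5.2 makes that model secondary. Section 5.1 does not list its Time levels; baseline and T1 are inferred from its stated aim, the effect after 4 weeks.

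A reader might also infer that r = 0.1 contradicts Section 3.1.1. It does not. That section names statistical analysis as well as repeated measurement and says nothing about shares of variance. Subtracting baseline removes any additive stable characteristic whatever r is; a low r costs precision, not control of confounding. There is a tension between planning on change and assuming nearly unrelated visits, but no conflict of text.

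Nor is r the only unsourced input: f is merely labelled medium, and the 10% dropout has no source either. A condensed article may leave a citation to the full protocol, and nothing shown proves 0.1 wrong. These points stand.

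They do not rescue the printed figure. The article itself states the inputs, the result and the assurance, and the result is the power of a test other than the one Section 5.1 describes.

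**Conclusion.** The point holds in this form: the 80% in Section 4.4 is correct for the run made, but it is not the power of the planned baseline-to-T1 Group × Time test at the stated r = 0.1. That power is about 76% under G*Power's default definition of f, and about 24% if f = 0.25 is a T1 difference in single-visit SDs. The shortfall is therefore small or large depending on a definition the article does not give. At higher r the planned test gains: 86%, 95% and over 99% under the first definition, and about 30%, 41% and 62% under the second, at r = 0.3, 0.5 and 0.7.

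These figures assume 66 patients analysed, equal groups, equal variances, one correlation between visits and α = 0.05 for a single outcome. The second definition also assumes no baseline difference. They do not show that the trial is underpowered; they show that the stated power is unsupported for the test that will be used.

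**What to change.** Keep N. In Section 4.4, replace the single power figure with a short table for the planned baseline-to-T1 Group × Time contrast at r = 0.1, 0.3, 0.5 and 0.7 for each primary outcome, and state how f is defined. Cite a visit-to-visit correlation for plasma BDNF, EV-derived BDNF and BADS where one exists. Remove the closing assurance of adequate power unless the table supports it.

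Optionally, around the 50% enrolment point of Section 5.3, estimate r and the SD from pooled, arm-blind T0 and T1 data and restate the detectable difference. This would be an addition: Section 5.3 plans a look at data accumulation and efficacy, not this estimate. Only patients who have reached T1 can contribute.

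The cost is one table, a few sentences and, if adopted, one blinded calculation on data already collected. The stated power may become less favourable.
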